### Primary and Secondary Outcome Measures

The primary study outcome will be children’s overall development at the age of 2.5 years. Children’s development will be assessed using the long form of the Global Scales for Early Development (GSED) [38]. The GSED is a new global open access tool designed to provide a standardized method for measuring the development of children up to 36 months of age in low-resource settings. We will use the long form of the GSED tool, which allows for a direct assessment of children’s development through trained assessors.

Secondary outcomes include (1) caregiver-reported early child development in motor, cognitive, language, and socio-emotional domains; (2) quality of a caregiver-child relationship; (3) screen time with and without a child being present; (4) primary female caregiver’s parenting behaviors; (5) parenting attitudes; and (6) mental health. Table 1 summarizes the measures to be collected at baseline and endline—all measures will be applied to the full sample, that is, to all participants independent of their random group assignment. Given that children were very young at baseline (6 months on average), detailed assessments of child development and caregiver-child interactions seemed unlikely to yield much insight at baseline. For overall child development, we used a caregiver report (Caregiver Reported Early Development Instruments [39]) at baseline and will use a more detailed direct observation tool (GSED) at endline. Sociodemographic factors collected at baseline will be used as controls in the final analysis.

**Table 1 table1:** Overview of constructs and measures used at baseline and endline.

Construct and measures		Time of assessment
**Child development (assessment)**		
	Child assessment (GSED^a^ Long Form) [38]	Endline
**Child development (parent report)**		
	CREDI^b^ Long Form [39]	Baseline
	CREDI Short form [39]	Endline
**Parent-child relationship quality**		
	Observation of Mother-Child Interaction [40]—adapted version	Endline
	ARI‐CP 2-5^c^ questionnaire [41] adapted short form	Endline
**Child information**		
	Nutrition, health and health insurance status, participation in ECD^d^ programs	Baseline and endline
**Anthropometrics**		
	Child weight at birth (reported)	Baseline
	Child weight and height (measured)	Endline
**Household demographics**		
	Household composition and assets; education, age, and so on of mother and father	Baseline
**Economic activity**		
	The main occupation for parents, membership in government support programs and COVID-19 support	Baseline
**Negative household events**		
	Household shocks questionnaire	Endline
**Phone network or internet availability and use**		
	Availability of phone, knowledge and use of apps, money spent on the phone, and phone use	Baseline
**Digital literacy**		
	Digital Literacy Scale [42]	Baseline
**Satisfaction with Afini (Afini group) and phone use**		
	Use and satisfaction with Afini and phone use	Endline
**Stimulation materials and experiences**		
	Family Care Indicators [43]	Baseline and endline
**Parenting behaviors, attitudes, and knowledge**		
	Parenting questionnaire (under development)	Endline
**Maternal social support**		
	Social support questionnaire	Baseline and endline
**Maternal mental health**		
	Depression, Anxiety, and Stress scale [44]	Baseline and endline
**Location**		
	GPS data	Baseline and endline

^a^GSED: Global Scales for Early Development.

^b^CREDI: Caregiver Reported Early Development Instruments.

^c^ARI‐CP 2-5: Attachment Relationship Inventory Caregiver Perception 2-5 years.

^d^ECD: early childhood development.

### Data Collection

#### Baseline Assessments

Upon caregivers’ consent, all caregivers completed a baseline survey, including household demographics, household structure, household poverty and income, educational attainment, child assets, household member interactions with the child, caregiver mental health, social support, and digital literacy. The baseline survey also collected data on the child’s age, sex, twin status, gestational length, birthweight, and attendance of daycare or other child- and household-supporting services as well as children’s early development using the Caregiver Reported Early Development Instruments tool [39].

#### End-of-Study Assessments

The endline surveys will occur when children reach 2.5 years of age, which will begin in September 2023. Table 2 shows an overview of the study timeline.

**Table 2 table2:** Study timeline and project activities.

Time period	Description of project activities
July 2020 to January 2021	Study setup, software development, and ethics board approval
February to July 2021	Field testing and finalizing tool development and high-frequency feedback to the programming team
September 2021 to March 2023	Enrollment and baseline survey of 2471 small children and their caregivers in the main trial plus 237 small children and their caregivers in the comparison group (total 2708 project participants)
September 2021 to August 2024	Parenting interventions
August 2023 to September 2024	Endline survey and assessments
October 2024 to February 2025	Data analysis
March 2025	Study dissemination event

The end-of-study assessment will involve gathering information on child development, maternal mental health, mother-child interactions, and parenting attitudes toward the child. To measure the primary outcome, we will use the GSED assessment tool [38]. Secondary outcomes include (1) caregiver-reported early child development in motor, cognitive, language, and socioemotional domains; (2) the quality of a caregiver-child relationship; (3) screen time with and without the child being present; (4) primary female caregiver’s parenting behaviors; (5) parenting attitudes; and (6) mental health. Table 1 provides details on the instruments used.

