**Results:**

Enrollment started in September 2021 and ended in March 2023. Endline assessments will take place between August 2023 and September 2024.

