### Sample Size Calculations

The study is powered to detect a 0.25 SD difference in normalized child development *z* scores (mean 0, SD 1) at the age 2 years between the Afini group and the control group and a difference of 0.5 SD in *z* scores between the home visit group and the control group. These calculations are based on the following assumptions: (1) an average of 15 (SD 5) children per village or study cluster, (2) an intraclass correlation of 0.12, (3) α=.05, and (4) an attrition rate of 15%. The estimated normalized effect size of 0.5 SD was based on 2 recent reviews of ECD home visiting programs [10,16]. We conservatively anticipate the Afini platform to only reach about half the target population and, thus expect an intention-to-treat effect size of 0.25 SD. Our assumptions regarding intraclass correlations, number of children per cluster, and attrition rates are based on a recently completed ECD-focused study in the same area [17].

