### Recruitment

Recruitment occurred continuously over 18 months with a target to enroll 2460 caregiver-child dyads. To identify potential children, the local health facilities’ birth registries from San Marcos, Cajamarca, and Cajabamba were used. All children between 3 and 9 months of age identified during the recruitment period in the study catchment area were eligible. All families that complied with the eligibility criteria were visited in person by study staff and invited to participate. The only reasons for exclusion were if the (1) caregiver and child intended to migrate outside the study area within the next 12 months, (2) child had a diagnosis of congenital abnormalities or a disability such as deafness or blindness (as reported by the caregiver), and (3) child already participated in the national PNCM program and did not belong to the PNCM comparison group. The study was built on a long-standing relationship of the research team with the regional and local health centers that facilitated recruitment.

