## Results

As shown in Table 2, enrollment and baseline data collection were completed in March 2023, and endline assessments were launched in September 2023. Table 4 shows descriptive statistics for the baseline sample by study arm. On average, children were 5 months old at baseline, 49.9% (1223/2452) were female, 8.1% (199/2452) had low birthweight (<2500 g at birth), and 97.5% (2391/2452) of children had a child health card. On average, mothers were 28 years old and considered literate. Fathers were slightly older, with an average age of 31.5 years at baseline, and had slightly higher education levels than mothers. The average household consisted of 2.5 adults and 1 additional child (sibling).

**Table 4 table4:** Descriptive statistics.

Characteristics	Control (n=962)				Home visits (n=315)				Afini (n=1175)		
	Observations, n	Clusters, n	Mean (SE)	Observations, n		Clusters, n	Mean (SE)	Observations, n		Clusters, n	Mean (SE)
Child age (months)	959	67	5.0 (0.11)	315		19	5.1 (0.22)	1169		78	5.1 (0.10)
Child is female	954	67	0.51 (0.02)	314		19	0.48 (0.03)	1172		78	0.50 (0.01)
Child has a health card	959	67	0.98 (0.01)	315		19	0.97 (0.01)	1169		78	0.98 (0.01)
Child born <2500 g	949	67	0.08 (0.01)	308		19	0.10 (0.02)	1152		78	0.08 (0.01)
CREDI^a^ score	950	67	43.0 (0.066)	307		19	43.0 (0.163)	1163		78	43.2 (0.065)
Mother’s age (years)	945	67	27.7 (0.26)	311		19	28.6 (0.48)	1155		78	28.0 (0.22)
Mother is literate	941	67	0.98 (0.01)	307		19	0.97 (0.01)	1151		77	0.99 (0.004)
Mother education level	944	67	3.2 (0.08)	310		19	3.2 (0.23)	1154		78	3.4 (0.08)
Father’s age (years)	843	66	31.2 (0.26)	277		18	32.1 (0.52)	1027		76	31.6 (0.26)
Father is head of household	844	66	0.94 (0.01)	277		18	0.94 (0.02)	1026		76	0.94 (0.01)
Father education level	832	66	3.5 (0.07)	267		18	3.5 (0.22)	1007		76	3.7 (0.07)
SES^b^ index	957	67	2.9 (0.12)	315		19	3.1 (0.29)	1169		78	3.2 (0.12)
Stimulation index	868	66	3.4 (0.06)	285		19	3.4 (0.14)	1076		78	3.5 (0.06)

^a^CREDI: Caregiver Reported Early Development Instruments.

^b^SES: socioeconomic status.

We anticipate completing the endline assessments in September 2024 and presenting final trial results to the local and national governments in Peru in early 2025.

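### The stated calendar closes endline before late-enrolled children can reach 2.5 years, the age at which the primary outcome is defined

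*Protocol article*

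**What the plan says.** - **Endpoint age.** Primary and Secondary Outcome Measures: "The primary study outcome will be children’s overall development at the age of 2.5 years". End-of-Study Assessments schedules endline by the same age: "The endline surveys will occur when children reach 2.5 years of age, which will begin in September 2023".
- **Entry age.** Recruitment: "All children between 3 and 9 months of age identified during the recruitment period in the study catchment area were eligible". Table 4 gives mean baseline ages of 5.0 to 5.1 months by arm; the outcome section mentions 6 months.
- **Calendar.** Abstract, Results: "Enrollment started in September 2021 and ended in March 2023. Endline assessments will take place between August 2023 and September 2024". The main Results section repeats the closing month: "We anticipate completing the endline assessments in September 2024". Table 2 gives the same window and starts data analysis in October 2024. Table 3 marks endline data collection only to the third quarter of 2024.
- **Text that points elsewhere.** Sample Size Calculations states the detectable difference "at the age 2 years between the Afini group and the control group". Statistical Analysis defines home visit compliance over an 18-month intervention period, while Home Visit Intervention Group describes visits from 6 months to about 2.5 years of age. The Home Visits section has the last household leaving in late 2024 and recruitment complete in January 2021, before it began. Table 2 ends the interventions in August 2024; Table 3 marks them through the fourth quarter of 2024.

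**The concern.** The age at assessment is part of the primary endpoint. If the calendar is followed, a late-enrolled child is either assessed well short of 30 months, after less exposure, or has no 2.5-year outcome. The article does not say which. In the first case the reported effect is an average over a spread of ages and exposure times and no longer the effect at 2.5 years. The sample-size age and the 18-month compliance period suggest that parts of the text were written for a different endpoint age, so a reader cannot tell which definition governs.

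**Working it through.** **Check of the plan's own figure.** (72 + 20 + 72) clusters × 15 children = 2460, which reproduces the recruitment target. Power is not stated. At the stated inputs (15 per cluster, SD 5, ICC 0.12, 15% attrition, two-sided α of .05 assumed) it comes to about 92-93% for 0.25 SD with 72 v 72 clusters, and above 99% for 0.5 SD with 72 v 20. The number enrolled is not the issue.

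**Timeline.** Count months from 1 September 2021. Let *e* be the enrolment month and *a* the age at enrolment. The end of March 2023 is month 19 and the end of September 2024 is month 37.

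Age at close = *a* + 37 − *e*.

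*Without any accrual assumption:*
- Enrolled at the end of March 2023 at 3 months: 3 + 37 − 19 = 21 months at close. At 9 months: 9 + 37 − 19 = 27 months.
- Reaching 30 months requires *e* ≤ *a* + 7. For the oldest entrant (*a* = 9) this is month 16, the end of December 2022.
- At the other end, a child enrolled at 9 months on 1 September 2021 is 9 + 24 = 33 months old on 1 September 2023.
- Time from enrolment to close is 37 − 19 = 18 months for the last enrolees. A child of mean age enrolled at the start reaches 30 months after 30 − 5.05 ≈ 25 months.

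*Assuming uniform accrual:*

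Share under 30 months = (19 − (*a* + 7)) / 19 = (12 − *a*) / 19.

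- *a* = 5.05 (Table 4): 6.95 / 19 = 0.366, about 900 of 2471 children.
- *a* = 6, or ages uniform on 3-9: 6 / 19 = 0.316.
- Extremes: all at 3 months, 9 / 19 = 0.474; all at 9 months, 3 / 19 = 0.158.

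**Other readings of the dates** (*a* = 6 to *a* = 5.05):

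| Reading | Formula | Share under 30 months |
|---|---|---|
| Enrolment ends at start of March 2023 | (11 − *a*) / 18 | 28-33% |
| Close at start of September 2024 | (13 − *a*) / 19 | 37-42% |
| Close at end of December 2024 | (9 − *a*) / 19 | 16-21% |
| Recruitment ends January 2023 (assumed) | (10 − *a*) / 17 | 24-29% |
| January 2023 end and December 2024 close | (7 − *a*) / 17 | 6-12% |

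**Tolerance around 2.5 years** (end of March 2023, end of September 2024). Accepting 29 months gives (11 − *a*) / 19 = 26-31%. Accepting 28 months gives (10 − *a*) / 19 = 21-26%.

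**The case against.** The strongest reply is that the document contains a later date. The Home Visits section has the last household completing endline in late 2024, Table 3 marks both interventions in the fourth quarter of 2024, and the September 2024 completion is only anticipated. This stands in part: with a close at the end of December 2024 the share falls to 16-21%. But it does not reach zero, and the late-2024 wording conflicts with Table 2, with the endline row of Table 3, and with both Results statements. The same section misdates the end of recruitment. Reading that as January 2023 is a guess against several statements of March 2023.

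It is also fair that 30 months need not be a hard limit, since the home visit description says approximately 2.5 years, and that uniform accrual is unverified. The share is therefore a range, not a known third.

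Three stronger readings are tempting and should not be drawn:

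- **Bias between arms.** A reader might infer that the age spread distorts the comparison. Clusters were randomised before enrolment, enrolment grew in all arms together, and mean baseline age is 5.0, 5.1 and 5.1 months. A difference in enrolment timing would carry over into age and exposure, but none is shown.
- **Loss beyond the assumed 15% attrition.** A reader might count the younger children as lost. No passage says that children under 30 months are dropped.
- **A wrong sample size.** The effects are in SD units, so the stated age does not enter the calculation.

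Finally, 21 to 33 months lies within the GSED's range of up to 36 months, and the outcome is already a z score against a global reference. The article does not say whether that score is age-standardised, so no bias can be quantified. Standardising would deal with differences in level by age; it would not make the outcome a 30-month one or equalise exposure.

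**Conclusion.** The point holds as an inconsistency in the primary endpoint. On the March 2023 and September 2024 dates, assessment at 2.5 years is impossible for every child enrolled after December 2022, whatever the accrual pattern. The proportion affected depends on assumptions: about 36-37% with uniform accrual, mean entry age of about 5 months and month-end dates, with the alternatives tabulated above. The two readings that also move the end of recruitment to January 2023 rest on a guess. The consequence is a change in the quantity estimated, to an effect averaged over about 21 to 33 months of age and over differing exposure. The documents do not support a claim of biased arms, excess attrition or inadequate power. The sample-size age and the 18-month compliance period are further signs that the endpoint age was not carried consistently through the text.

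**What to change.** - Restate the primary endpoint as the GSED z score at endline, say that it is age-standardised, and give the age window that the calendar actually delivers.
- Include age at assessment as a covariate in the primary model.
- Report age at assessment and exposure time by arm.
- Correct the age in Sample Size Calculations so that it matches the endpoint.
- Reconcile the endline, intervention and compliance periods across Home Visit Intervention Group, End-of-Study Assessments with Table 2, Home Visits with Table 3, and Statistical Analysis, including the January 2021 and late-2024 dates. Which intervention period or compliance rule applies is for the investigators to settle.

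The cost is wording, one more covariate and two descriptive summaries. No new participants or visits are needed. The downside is a less specific endpoint label than development at 2.5 years.

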### Additional Data Collection

To monitor and ensure the quality of the Afini platform, we collect data on users’ platform usage and interactions with the system for the Afini group. These data include activities dispatched to the users, users’ ratings, and feedback on the activities and questions asked. This data access is restricted to the service developers and maintainers and associated with an anonymized internal ID. Through these data, we identify users that have been “recently active” in the platform, which we define as having interacted with the service in any way in the past 15 days. A randomly selected subset of households in the Afini group, qualifying as “recently active,” receives a small biweekly data credit transfer (US $0.8 to US $2.0) to evaluate a potential increase in the use of the platform through small rewards. The data transfer cost and value depend on the service provider (Claro and Bitel) and the aggregator used to perform the credit transfer (Reloadly and DTOne), with these costs increasing within that range from the start of the reward program.

### Home Visits

For each home visit, a short visit form was completed to document the time and date, topics covered, and toys delivered. Additionally, we collected information about the play environment, the toys available, and the interactions between the caregiver and the child at the time of the visit.

Table 3 provides an overview of all study activities. Recruitment and baseline surveys started in the third quarter of 2021. Given the prerandomization of clusters to treatment, interventions were initiated directly after baseline in September 2021, gradually increasing sample sizes in all arms. Recruitment was completed in January 2021, and the first households were scheduled to complete the endline assessment (and exit the study) in September 2023. Interventions will continue (with a steadily decreasing number of households) until the last household completes the endline survey and exits the study in late 2024.

**Table 3 table3:** Overview of study activities^a^.

Study activity		Year and quarter																		
		2021					2022					2023					2024			
		1	2	3	4	1		2	3	4	1		2	3	4	1		2	3	4
**Data collection**																				
	Baseline survey			✓	✓	✓		✓	✓	✓	✓									
	Afini user data collection			✓	✓	✓		✓	✓	✓	✓		✓	✓	✓	✓		✓	✓	
	Home visit logs			✓	✓	✓		✓	✓	✓	✓		✓	✓	✓	✓		✓	✓	
	Endline data collection													✓	✓	✓		✓	✓	
**Interventions**																				
	Home visits			✓	✓	✓		✓	✓	✓	✓		✓	✓	✓	✓		✓	✓	✓
	Afini system use			✓	✓	✓		✓	✓	✓	✓		✓	✓	✓	✓		✓	✓	✓

^a^Summarizes data collection and intervention activities. Each cell corresponds to a quarter in the 2021-2024 period. Active data collection periods and active intervention periods are marked with a ✓.

### Statistical Analysis

After confirming the psychometric reliability and validity of our key variables, we will perform a descriptive analysis (means and percentages) for the main characteristics and calculate prevalence and proportions for the primary outcomes. We will use standard linear regression models to assess the impact of the 2 intervention arms on child development. The primary outcome variable will be overall development as measured by the GSED, normalized to a developmental *z* score with a mean (0, SD 1) in the global reference population. Our primary empirical approach will be intent-to-treat, that is, comparing average outcomes across the 3 arms (independent of intervention compliance) with average outcomes in the control group. We will also conduct additional per-protocol analyses measuring mean differences between compliant children in the intervention arms with compliant children in the control group. For the home visit group, compliance will be defined as receiving at least 18 out of the 36 anticipated visits over the 18-month intervention period. Compliance with the Afini intervention will be defined as having interacted with the system at least once per month for at least 6 months in the observation period. Cluster-robust standard errors will be used to account for the cluster-level randomization of the intervention. Separate models will be estimated with and without baseline covariates.

Specifically, we will assess and control for household factors, caregiver factors, and child factors. Structural equation modeling will be used to test subgroup and mediation effects.

We will calculate the intervention’s cost-effectiveness by comparing the developmental outcomes observed in the 2 intervention arms to the average developmental levels in the control arm to the costs of the 2 interventions per child.

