### Description of the Study Groups and Intervention

#### Control Group

The control group comprises families that receive the regular level of mother and newborn child health care in the region. They have not been benefitting from any ECD program or intervention, but they may have sought assistance regarding parenting from within their network. This study group is only visited once at the beginning (baseline survey) and once at the end of the study (endline survey and assessment).

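### The per-protocol contrast has no control counterpart to its compliers, so it is non-randomised and probably favours the interventions

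*Protocol article*

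**What the plan says.** The protocol article's Statistical Analysis section makes intention-to-treat the primary approach and adds per-protocol analyses "measuring mean differences between compliant children in the intervention arms with compliant children in the control group". It then defines compliance twice, each time by the amount of intervention received:

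- Home visits: "compliance will be defined as receiving at least 18 out of the 36 anticipated visits over the 18-month intervention period".
- Afini: "having interacted with the system at least once per month for at least 6 months in the observation period".

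No definition follows for the control arm. The Control Group section says of these families: "They have not been benefitting from any ECD program or intervention, but they may have sought assistance regarding parenting from within their network". It adds: "This study group is only visited once at the beginning (baseline survey) and once at the end of the study". Under Additional Data Collection, usage is recorded in one arm only: "we collect data on users’ platform usage and interactions with the system for the Afini group".

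Two other statements bear on the point. Table 1 records, at baseline and endline, "Nutrition, health and health insurance status, participation in ECD" programmes, and the outcome section applies the Table 1 measures to all arms. The Statistical Analysis section also plans models with and without baseline covariates.

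**The concern.** A per-protocol comparison is interpretable only if the two sides are selected in the same way. Here one side consists of families who kept using the chatbot or accepted at least half the visits. The other side was never offered anything by which the same kind of family could be recognised. Families who persist are likely to differ from those who do not in education, means, connectivity and motivation, and these may also relate to child development. The difference in means then mixes the effect of the intervention with the difference between the families.

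This matters because the sample-size section itself expects Afini to reach only about half of its target population. The effect among actual users is therefore an obvious follow-up question, and the per-protocol contrast is the analysis the article offers for it.

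**Working it through.** **1. The plan's own figures.** The Sample Size Calculations section takes 0.5 SD as the full effect and about half as the Afini reach: 0.5 × 0.5 = 0.25 SD, which is the stated intention-to-treat effect. The enrolment target also reproduces: 164 clusters × 15 children = 2460.

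**2. Who could be a compliant control?**

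| Possible meaning | Data in controls | Matches the intervention compliers? |
|---|---|---|
| Met the visit or usage threshold | None; no exposure delivered | Not possible |
| Would have met it if offered | Unobservable | Yes, but cannot be identified |
| Stayed out of other ECD programmes | Table 1, baseline and endline | No; a different trait |
| All controls | Available | No; unselected |

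Only the last two can be carried out, and neither selects controls on engagement.

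**3. Size of the bias with no true effect.** Let c be the share compliant and d the outcome difference, absent any intervention, between would-be compliers and the rest. Compliers differ from controls not selected on engagement by (1 − c)d. If engagement propensity and outcome are bivariate normal with correlation r and the top half comply, the shift is r × φ(0)/0.5 = 0.798r.

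Assumptions: c = 0.5, borrowed from the anticipated Afini reach, and r = 0.1 to 0.3. The documents give neither r nor the share that would meet the compliance definition.

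| r | Bias (SD) | Share of 0.25 SD | Implied d = 1.596r |
|---|---|---|---|
| 0.1 | 0.080 | 32% | 0.16 |
| 0.2 | 0.160 | 64% | 0.32 |
| 0.3 | 0.239 | 96% | 0.48 |

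Setting d directly to 0.1, 0.2, 0.3 or 0.4 SD gives 0.05, 0.10, 0.15 or 0.20 SD. The share compliant matters too: with d = 0.2 the bias is 0.14 SD at c = 0.3 and 0.06 SD at c = 0.7. All of these are before covariate adjustment.

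**4. False-positive rate of the unadjusted contrast.** Inputs: 72 clusters per arm; 15 × 0.85 = 12.75 children per cluster after attrition; ICC 0.12; cluster-size CV 5/15; two-sided 5% (sidedness assumed). The design effect for controls is 1 + (1.111 × 12.75 − 1) × 0.12 = 2.58. For compliers, at 6.375 per cluster, it is 1.73. The standard error is √(2.58/918 + 1.73/459) = 0.081. With no true effect, the test rejects in about 9.5%, 23%, 46% and 69% of trials for d = 0.1, 0.2, 0.3 and 0.4.

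**5. The randomised alternative.** The instrumental-variable estimate is the intention-to-treat effect divided by uptake. At 50% uptake, 0.25/0.5 = 0.50 SD. The Discussion reports that 84% of pilot mothers had used the platform at least once. With any use as exposure at that rate, 0.25/0.84 = 0.30 SD. The figure depends on how exposure is defined, but no control complier has to be identified.

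**The case against.** The strongest reply has three parts.

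- **A meaning exists.** In an untreated arm, per-protocol usually means remaining untreated. The government programme partly covers the area, participation is recorded in every arm, and a control family that joined would be a departure from protocol. This stands: a reader might infer that compliant controls cannot be defined at all, and the documents do not support that. What cannot be identified is the control counterpart of the engaged families, and excluding programme users does not supply it.
- **Adjustment is planned.** Table 1 has parental education, assets, phone and internet access, and digital literacy at baseline. These cover much of the likely selection, so the unadjusted figures overstate what would remain. This also stands, but caregiver motivation is not measured and models without covariates are planned as well.
- **It is a secondary analysis in a condensed article.** Full definitions may sit in a document not shown. The first half is right and limits the severity. The second does not dispose of the point, because the article itself fixes the contrast and both thresholds.

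A reader might also infer that the bias is certain to favour the interventions, or that it amounts to most of the target effect. The documents give neither sign nor size. An upward bias is the probable direction, the lower end of the assumed range is 32%, and r = 0.3 would require a gap of about 0.48 SD between families before any treatment.

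**Conclusion.** The per-protocol contrast, as fixed in the article, sets families selected on sustained engagement against controls who are not so selected. It is non-randomised and probably biased towards the interventions. Under assumed 50% compliance and r between 0.1 and 0.3, the unadjusted bias with no effect is 0.08 to 0.24 SD, and smaller by an unknown amount after adjustment.

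The point does not touch the trial's main conclusion. Intention-to-treat is primary and does not use compliance. Nor do the documents say that the per-protocol result will be presented as the headline effect in users. It should be corrected before analysis, but it does not threaten the design.

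**What to change.** Make the compliance-related causal estimate an instrumental-variable analysis of each intervention arm against control, with randomised arm as instrument and the same covariates and cluster-robust errors as the intention-to-treat model.

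- **Main version:** any use (Afini) or any visit (home visits) as the binary exposure, giving a complier average causal effect.
- **Secondary version:** active months or number of visits, reported as a weighted average per-unit effect, not as a complier effect.
- **Avoid** the 6-month or 18-visit threshold as the exposure. Families below it may still benefit, and that benefit would be credited to those above it.
- **State the assumptions:** assignment acts only through the exposure, and controls have none of it.

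If the per-protocol contrast is kept, say that control compliance means no outside ECD programme, report it covariate-adjusted, and label it non-randomised and descriptive.

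While that paragraph is open, its 36 visits over 18 months should be reconciled with the Home Visit Intervention Group section. That section describes visits every 2 weeks from 6 months to about 2.5 years of age, roughly 24 months.

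The cost is one extra model and wider intervals; usage data and visit logs are already collected. Roughly, the intention-to-treat standard error of 0.075 (inputs as in step 4) becomes 0.075/0.84 = 0.089 at 84% uptake or 0.075/0.5 = 0.150 at 50%, against 0.081 for the complier contrast.
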